### Sample size estimation

We expect to find small mean differences between WMR and CMR in primary outcomes. For three months, of about 18,000 insured patients with permission for a musculoskeletal rehabilitation program 15,000 will receive CMR and 3,000 will receive WMR. We expect a participation rate of 40 %, i.e. 7,200 patients (6,000 CMR, 1,200 WMR) at baseline. At the 10-month follow-up, we expect a dropout rate of 25 %, i.e. 900 patients with WMR and 4,500 CMR left. Using a one-to-one match without replacement, 1,800 patients (900 WMR, 900 CMR) will be analyzed. Assuming a number of clusters (departments) *k* = 256 (with 176 departments providing CMR and 80 departments providing additionally WMR), a cluster size of *m* = 7.0, an intracluster correlation of rho = 0.05, a power of 0.80 and a Bonferroni corrected *p*-value = 0.016, an effect of SMD = 0.175 can be detected (Fig. 1).

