#### Primary outcomes

The primary outcomes of this study are sick leave duration, stable return to work, and subjective work ability. Evaluation of the effectiveness of WMR relates to the 10-month follow-up. These three outcomes will also be assessed at the three-month follow-up and if appropriate at baseline.

To assess the duration of sick leave, the participants will be asked to report the number of weeks they have been off work for health reasons since discharge from the rehabilitation center. At baseline this question is related to the last 12 months. Stable return to work has been defined in accordance with Kuijer and colleagues [27] as a minimum of four weeks of employment without sick leave. Subjective work ability will be assessed by the Work Ability Score (WAS), which is the first item of the Work Ability Index (WAI) [28]. It compares current subjective work ability with the lifetime best. The 11-point scale ranges from zero (complete incapacity to work) to ten (lifetime’s best work ability). The WAS is highly correlated with the overall WAI score [29].

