#### Multilevel regression analyses

Analyses of treatment effects in propensity score matched samples can use the same statistical methods as those used in experimental studies [48, 49]. Multilevel regression analyses will be used to account for dependencies in the data [57, 58]. Individual patient data will be conceptualized as level-1 parameters and the rehabilitation department as a level-2 variable. All models will include the treatment variable (WMR vs. CMR), the baseline score of the respective outcome measure and a random intercept which reflects the rehabilitation department. For the primary outcomes, p-value will be fixed at 0.016 (Bonferroni corrected for three outcomes). For the secondary outcomes, p-value will be fixed at 0.05. Linear models will be used for continuous outcomes and logistic models for binary outcomes.

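### Fixed single-step Bonferroni testing of the three primary outcomes is valid, but Holm's step-down test would recover power at the same 5% family-wise error

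*Protocol article*

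**What the plan says.** In the Protocol article, the Primary outcomes section names three outcomes: "The primary outcomes of this study are sick leave duration, stable return to work, and subjective work ability", evaluated at the 10-month follow-up. The closing paragraph of the Background hypothesises that WMR is better than CMR on all three.

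The Multilevel regression analyses section sets one threshold for each of them: "For the primary outcomes, p-value will be fixed at 0.016 (Bonferroni corrected for three outcomes"). Secondary outcomes are tested at 0.05. The overall level for the primary family is not put into words; 5% is implied by the Bonferroni wording and by the level used for secondary outcomes.

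The Sample size estimation section plans on the same threshold, with "a power of 0.80 and a Bonferroni corrected" p-value of 0.016, and concludes that "an effect of SMD = 0.175 can be detected". No step-down or other sequential procedure is mentioned.

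**The concern.** Single-step Bonferroni protects against three false nulls for every test, even after one null hypothesis has been rejected. Once one is rejected, at most two remain to be protected, so the next p-value can be compared with 0.05/2 and the last with 0.05. Holm's procedure does this. It needs no assumption about how the outcomes are related, and it cannot reject less than Bonferroni does.

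The study hypothesises benefit on all three outcomes, which is the setting in which the fixed rule gives away most. At stake is the chance that a second or third true effect is declared not significant although the same data, at the same family-wise error, would have supported it.

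**Working it through.** **Inputs.** All but the last come from Sample size estimation.
- Analysed sample, after dropout: "Using a one-to-one match without replacement, 1,800 patients (900 WMR, 900 CMR) will be analyzed".
- "an intracluster correlation of rho = 0.05" and a cluster size of 7.0.
- "a power of 0.80", per-outcome level 0.016, SMD 0.175.
- The correlation between outcome test statistics is not in the document. It is assumed equal for all pairs and varied over 0, 0.3, 0.5 and 0.7.

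**1. The plan's own figure.** Design effect = 1 + (7 − 1) × 0.05 = 1.30. Standard error of the SMD = √(2 × 1.30/900) = 0.0537. Detectable SMD, two-sided = (2.409 + 0.842) × 0.0537 = 0.1747. This reproduces the stated 0.175. Power at 0.175 and level 0.016 is 0.8015.

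**2. The rounding of the level.** 0.05/3 = 0.0167, so 0.016 is slightly too small (3 × 0.016 = 0.048). Power is 0.8015 at 0.016 and 0.8056 at 0.0167; the detectable SMD is 0.1747 against 0.1739. This is immaterial.

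**3. Power at Holm's later steps.** At SMD 0.175, power for a given outcome is 0.845 at level 0.025 and 0.903 at level 0.05.

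**4. All three confirmed, zero correlation.**
- Plan: 0.8015³ = 0.515.
- Holm: let a = 0.8056 (p at or below 0.0167), b = 0.8448 − 0.8056 = 0.0392 (p between 0.0167 and 0.025) and c = 0.9025 − 0.8448 = 0.0577 (p between 0.025 and 0.05). All three are rejected with probability a³ + 3a²(b + c) + 3ab² + 6abc = 0.523 + 0.189 + 0.004 + 0.011 = 0.726 before rounding of the terms.

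**5. Simulation across correlations.** One million draws of three test statistics per setting, each real effect at SMD 0.175. Ranges cover correlations 0 to 0.7.

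| Real effects | Quantity | Plan (0.016) | Holm (5%) |
|---|---|---|---|
| Three | Power per outcome | 0.80 | 0.86–0.885 |
| Three | All three confirmed | 0.52–0.66 | 0.73–0.80 |
| Two | Power per outcome | 0.80 | 0.83–0.84 |
| Two | Both confirmed | 0.64–0.71 | 0.71–0.77 |
| Two | Null outcome rejected | 0.016 | 0.036–0.043 |
| One | Power for that outcome | 0.80 | 0.81 |

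Holm's simulated family-wise error was at most 0.049 in every configuration.

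**6. Direction of the correlation effect** (three real effects, all three confirmed).

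| Correlation | Plan | Holm | Gain |
|---|---|---|---|
| 0 | 0.52 | 0.73 | 0.21 |
| 0.3 | 0.57 | 0.75 | 0.18 |
| 0.5 | 0.61 | 0.77 | 0.16 |
| 0.7 | 0.66 | 0.80 | 0.14 |

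**7. At least one significant outcome.** Holm's first step is Bonferroni at 0.0167, so only the rounding changes. With three real effects and correlation 0.5, the probability goes from 0.951 to 0.952.

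**The case against.** The strongest reply is that nothing here is wrong. Bonferroni is valid under any dependence, the two sections use the same level, the detectable effect reproduces, and each outcome has 80% power at the level at which it will be tested. The cost was planned for. All of this stands, and it makes the point one of efficiency.

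Several further limits also stand.
- SMD 0.175 is what the plan says can be detected, not an effect predicted for each outcome. If all three effects were 0.25, power per outcome would already be 0.988 under the plan, against 0.995–0.996 with Holm.
- Stable return to work is binary and analysed by logistic regression, but the check puts it on the same standardized scale.
- Holm's family-wise control allows a higher rejection rate for a single null outcome when the other two effects are real. That deserves weight in a non-randomised study whose authors themselves regard allocation bias as a serious challenge.
- Fixed levels give simple simultaneous confidence intervals and keep each outcome's result independent of the others. The protocol does not offer this as its reason.

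A reader might infer more than the document supports:
- *That the study is underpowered or the correction faulty.* The plan meets its own 80% per outcome, and 0.016 errs on the safe side by a trivial amount.
- *That positively related outcomes make the loss worse.* The second table shows the reverse.
- *That success requires all three outcomes.* The hypothesis covers all three, but the plan powers and tests each separately.

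**Conclusion.** The point holds as a cheap improvement, not as an error in the plan. Holm is never less powerful than the fixed rule at the same 5% family-wise error, and that statement needs no assumption about correlation or effect size. How much it gains does depend on both. The gain is material when all three effects are real and near the detectable size, moderate when two are, and negligible when only one is or when the question is whether any outcome is significant. The work-related outcomes are plausibly positively correlated, so the lower gains in the ranges are the more relevant ones. The quoted figures further rest on equal effects, equal pairwise correlations and the plan's design effect of 1.3.

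**What to change.** Replace the sentence on the primary-outcome threshold in Multilevel regression analyses with:

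> The three primary outcomes are tested with the Holm procedure at a two-sided family-wise level of 0.05 (ordered p-values against 0.0167, 0.025 and 0.05).

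The sample size statement can stay, because 0.016 is a slightly conservative version of Holm's first step. No additional patients are needed.

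Make and date the change before outcome data are analysed. The Trial status section says recruitment is still under way, and the primary outcomes are measured ten months after discharge, so this is feasible at the stage described.

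There are two costs. Holm has no simple simultaneous intervals that match its decisions, so report Bonferroni intervals beside the tests and say that they may not agree with the Holm result. And a null outcome is rejected more often when the other two effects are real (about 3.6–4.3% against 1.6%), which is still within the 5% family-wise error.

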#### Moderator analyses

Exploratory moderator analyses will be performed to clarify whether level-1 or level-2 characteristics modify the treatment effect. The modeling of moderator effects of level-1 characteristics will be realized by multiplicative interaction terms of the treatment indicator and potential moderators. Moderator effects of level-2 variables will be tested by including the potential moderator as a level-2 predictor of the level-1 treatment-effect. In the case of continuous moderators, these variables will be z-standardized [59]. Level-1 moderators will be tested in order to identify patients who particularly benefit from WMR. Level-2 moderators may suggest department characteristics that may impact the effectiveness of WMR.

## Discussion

This study will provide an estimation of the relative effectiveness of a complex, newly implemented work-related rehabilitation strategy for patients with musculoskeletal disorders. Findings will complement the existing evidence of the relative efficacy derived from randomized controlled trials by robust estimation of the effects under real-life conditions of rehabilitation service provision in Germany. The findings of this study will be published in peer-reviewed journal articles and conference presentations.

## Trial status

Recruitment has started and is ongoing.

## Abbreviations

CMR, conventional medical rehabilitation; GAD-2, Generalized Anxiety Disorder Questionnaire; GPI, German Pension Insurance; IRES-24, Indikatoren des Reha-Status; PHQ-2, Patient Health Questionnaire; WAI, Work Ability Index; WAS, Work Ability Score; WMR, work-related medical rehabilitation
